### Primary Analysis

#### Case Definition

The medical products in the DNPR are coded in accordance with the Anatomical Therapeutic Chemical (ATC) system. In the present project, a person will become a case if and when he or she redeems a prescription for drugs in the ATC-code category N05 (psycholeptica) or N06 (psychoanaleptica). The psycholeptic category contains antipsychotics, anxiolytics, hypnotics, and sedatives, while the psychanaleptic category contains antidepressants, psychostimulants, and antidementia drugs.

#### Follow-Up and Inclusion Criteria

Each of the included samples will be followed for a period of two to five years, beginning at the start of the calendar year succeeding the one in which they were sampled. People should be between 21 and 59 years old at the start of the follow-up period and, according to the questionnaire, employed with 32 or more weekly work hours around the time of the interview, to be eligible for inclusion. The sample from DWECS 2010 will be followed for two years. The sample from the DANES 2008 will be followed for four years. The remaining samples will be followed for five years. A participant will be censored if and when he or she dies or emigrates. Person years at risk will be calculated for each participant. People who redeemed a prescription for a medication with an ATC-code that belongs to the case definition, during the calendar year preceding baseline, will not be included. A participant who reaches the clinical endpoint of the study will not be allowed to reenter the follow-up. In other words, there will be maximum one case per person.

#### Statistical Model

We will use Poisson regression to analyze incidence rates of redeemed prescriptions for psychotropic medicine as a function of weekly working hours (32-40; 41-48; > 48 hours/week). The analysis will be controlled for gender, age (10 year classes), sample (DWECS 1995; DWECS 2000; COPSOQ 2004; DWECS 2005; DANES 2008; and DWECS 2010), shift work (fixed night shifts or rotational shift work schedules vs other), and SES (legislators, senior officials and managers; professionals; technicians and associate professionals; workers in occupations that require skills at a basic level; workers in elementary occupations; and gainfully occupied people with an unknown occupation). With SES we mean socioeconomic status, according to the employment classification module, during the calendar year of the baseline interview. The logarithm of person years at risk will be used as offset. A likelihood ratio test will be used to test the null-hypothesis, which states that the analyzed rates are independent of weekly working hours. The significance level is set to 0.05.

#### Power Calculations

Based on rates calculated through DNPR in the time period 2001-2005, we expect on average approximately 25 new cases per 1000 person years at risk (PYRS). We expect that the four follow-up periods of nonprevalent cases in the DWECS samples will provide approximately 68,000 PYRS, the five year follow-up of the COPSOQ sample will provide 12,000 PYRS, and the four year follow-up of the DANES sample will provide 16,000 PYRS. Among the ones who worked 32 or more hours per week in 2000 according to DWECS, 26.7% worked more than 40 hours/week and 10.5% worked more than 48 hours/week.

With the above data as input, Figure 1 illustrates the statistical powers to detect contrasts between normal working hours (32-40 hours/week) on one hand and “overtime work” (>40 work hours/week), “moderate overtime work” (41-48 work hours/week), and “very much overtime” (49-100 work hours/week) on the other, as a function of the true rate ratio. If, for example, the true rate ratio between moderate overtime workers and those with normal working hours is 1.2 then we have a 90% chance of detecting the difference; if it is 1.3 then the chance of detection is 99.7%. The power calculations are based on the Poisson distribution, the propagation of error formulas, and the central limit theorem.

**Figure 1 figure1:**
[figure not shown]
Power of detecting differences in psychiatric morbidity rates in Denmark, between overtime workers and people with normal work hours, as a function of the true rate ratio.

#### Transitions Between Work Categories

The subjects of our study will be categorized according to their exposure status at baseline. They will thereafter be followed for five years. We do not have information about their work schedules during the follow-up, but wanted to ascertain that the exposure statuses were stable enough to make the study worth the while. To check this, we used DWECS data to cross-tabulate a worker’s exposure status in 2000 with that in 2005. We included all who were economically active and 30 years or older in both waves. The exposure statuses were fairly stable over time; 68.3% (529/774) of the workers with long working hours and 83.28% (1240/1489) of the workers with normal working hours in 2005 had the same working conditions five years earlier, while 67.9% (529/778) of the workers with long working hours and 83.50% (1240/1485) of the workers with normal working hours in 2000 had the same working conditions five years later. Cohen’s kappa for agreement between the working hour category in 2000 and in 2005 was 0.52 (95% CI 0.48-0.55), which indicates a moderate agreement according to Landis and Koch [36].

### Secondary Analyses

Regardless of whether or not the primary research hypothesis is confirmed, we will perform a series of secondary analyses. The interpretation of the results from these analyses will, however, depend on the outcome of the primary hypothesis test. If the primary null-hypothesis is rejected, then the secondary analyses will be regarded as nested hypothesis tests. Otherwise, they will be regarded as hypothesis generating exploratory analyses, whose results need to be confirmed in an independent dataset before they can be deemed statistically significant.

With the endpoint and covariates of the primary hypothesis test, we will use likelihood ratio tests to check for possible two-way interaction effects between working hours and gender, age, shift work (fixed night shifts or rotational shift work schedules vs other), or socioeconomic status. Subsample analyses will thereafter be performed on data stratified, first by gender, then by age (21-39; 40-59 years old), then by shift work, and finally by socioeconomic status. In keeping with the principles of nested hypothesis testing, perceived differences in effect sizes between strata will not be considered statistically significant unless both the primary hypothesis test and the concerned two-way interaction effect are statistically significant.

In addition to the above, we will perform three separate analyses, in exactly the same way as we did in the primary analysis, but with endpoints defined by the following subsets of ATC-codes, N05B (anxiolytics), N05C (hypnotics and sedatives), and N06A (antidepressants).

### Auxiliary Analysis Regarding Prescription Bias

Some people with sleeping disorders seek medical care to cope with the situation, while others do not. The same holds for anxiety and depressive disorders. We can therefore not know if an increased use of medicine is due to an increased need of treatment or an increased propensity to seek treatment. Our primary analysis will show if long working hours is associated with subsequent use of psychotropic medicine. Such a finding is of interest in itself. Obtained rate ratios can, however, only be interpreted as morbidity rate ratios if we can show that prescription bias is likely to be negligible.

Our data material allows us to evaluate whether or not prescription bias is present. The questionnaires that we describe in our project plan contain questions on mental health, which enable us to relate the prevalence of self-rated mental ill health to the prevalence of medicine users among people with long and normal working hours respectively.

In particular, the DANES questionnaire and the DWECS questionnaires of 1995, 2000, and 2005 contain all items needed to score the participants on the five item scale of the mental health inventory MHI-5, which is a subscale of the SF-36 general health index [37]. The MHI-5 scale is based on the following questions, all relating to the past four weeks: (1) “Have you been very nervous?”; (2) “Have you felt so down in the dumps that nothing could cheer you up?”; (3) “Have you felt calm and peaceful?”; (4) “Have you felt down-hearted and depressed?”; and (5) “Have you been happy?”. Each question should be answered with one of the following response categories; “all of the time”; “most of the time”; “a good bit of the time”; “some of the time”; “a little of the time”; or “none of the time”. The categories are scored, in the order listed, from 1 to 6 for the first, second, and fourth question, and from 6 to 1 for the third end fifth question. The score of the full scale is a function of the scores of the items, and ranges between 0 and 100. The equation reads y=100(x - n)/(5n), where y is the score of the full scale, n is the number of included items, and x is the sum of the scores of the included items. If the response is missing for two items or more then the whole scale will be categorized as missing. A lower score on the full scale indicates a poorer mental health, and a score which is less than or equal to 52 is regarded as an indicator of severe mental health problems [33,38,39]. The Danish translation of the SF-36 questionnaire has been validated [40] and the MHI-5 subscale has been shown to be reliable in the general population of Denmark (Cronbach alpha = 0.80) [41].

To shed some light on the matter of prescription bias, we will perform an auxiliary cross-sectional analysis, which compares odds ratios for poor self-rated mental health with odds ratios for use of psychotropic medicine among workers with long versus normal working hours. If either of these ratios is statistically significant, while the other one points in the opposite direction, then the idea that an increased/decreased rate of medicine usage can be interpreted as an increased/decreased rate of poor mental health is contradicted.

For this analysis, we will not include information from COPSOQ or DWECS 2010. Otherwise, the data sources are the same as the ones described for the primary analysis. Prevalent cases will not be excluded, but the rest of the inclusion/exclusion criteria will be the same as the ones of the primary analysis. The following case definitions will be employed for poor self-rated mental health and use of psychotropic medicine, respectively: (1) a score on the mental health inventory (MHI-5) that is less than or equal to 52, and (2) redemption of a prescription for a drug in the ATC-code category N05 (psycholeptica) or N06 (psychoanaleptica), during the calendar year of the interview.

Logistic regression will be used to model the odds of the outcomes as a function of weekly working hours (>40 hrs/week; 32-40 hrs/week). The analysis will be controlled for gender, age, socioeconomic status, shift work, and sample in the same way as was done in the primary analysis. Generalized estimating equations will be used to estimate the parameters. Observations from the same person will be treated as repeated measurements. A first order autoregressive correlation structure is assumed. The odds ratio (OR) between the exposed and the nonexposed will be calculated and presented with a 95% CI. The CI will be based on the empiric standard error. An OR will be considered statistically significant if the CI does not contain 1.

Approximately 16,500 employees will fulfill the inclusion criteria of this auxiliary analysis. The prevalence of poor self-rated mental health (MHI-5 ≤ 52) among Danish employees was estimated to 7.3% in 2008 [33], while the corresponding prevalence for use of psychotropic medicine was 9.3% (according to a linkage between the ECM and the DNPR). With such a frequency of events, we estimate that the power to detect an OR of 1.2 or higher or 1/1.2 or lower between employees with long versus normal working hours will be at least 80% for either of the two outcomes.

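### The prescription-bias rule can contradict a morbidity reading of the rate ratios but, because it never estimates how far the two odds ratios differ, it cannot show that the bias is negligible

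*Protocol article*

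**What the plan says.** The section Auxiliary Analysis Regarding Prescription Bias sets a condition: "Obtained rate ratios can, however, only be interpreted as morbidity rate ratios if we can show that prescription bias is likely to be negligible". It then asserts: "Our data material allows us to evaluate whether or not prescription bias is present".

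The analysis offered for this compares two cross-sectional ORs for more than 40 versus 32-40 hours per week. One is for poor self-rated mental health (MHI-5 of 52 or less), the other for redeeming an N05 or N06 prescription in the interview year. Each is estimated by GEE logistic regression and reported with a 95% CI, and "An OR will be considered statistically significant if the CI does not contain 1".

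The only decision rule takes effect in one situation: "If either of these ratios is statistically significant, while the other one points in the opposite direction". In that event, taking more (or less) medication use to mean more (or less) mental ill health counts as refuted. The aim is worded cautiously: "To shed some light on the matter of prescription bias". The article gives no estimate or CI for the difference between the two ORs, and does not say what follows when both lie on the same side of 1.

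**The concern.** The condition and the rule do not meet. The condition asks for positive evidence that bias is small. The rule can only deliver negative evidence, and only in one pattern: a sign reversal with one OR significant. For instance, an observed MHI-5 OR of 1.30 with a medication OR of 1.05 passes, although their ratio is 1.05/1.30 = 0.81.

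What is at stake is the size of the effect as a statement about mental ill health. The Conclusions in the Abstract promise to indicate both the extent and the direction of the influence of long hours on the national burden. The rule bears on direction only. Nothing else in the article is offered to meet the negligibility condition.

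**Working it through.** **Inputs from the article.** Auxiliary section: N about 16,500; prevalence 7.3% (MHI-5) and 9.3% (medication); design OR 1.2 or 1/1.2; claimed power at least 80% for each outcome; two-sided 5%. Power Calculations: 26.7% work more than 40 hours (DWECS 2000). The exposed share of the auxiliary sample itself is not given.

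**Assumptions.** Independent observations, no covariate adjustment, normally distributed log ORs, correlation ρ between the two estimates of 0 to 0.3.

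**Step 1: the article's own power.** Exposed n1 = 0.267 × 16,500 = 4,405.5; unexposed n0 = 12,094.5. For OR 1.2 at 7.3% overall, p0 = 0.0696 and p1 = 0.0824.

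SE(log OR) = √[1/(n1·p1(1−p1)) + 1/(n0·p0(1−p0))] = √(0.00300 + 0.00128) = 0.0654.

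Power = Φ(ln 1.2/0.0654 − 1.96) = Φ(0.83) = 79.6% (78.8% by the pooled two-proportion formula). For medication it is 86.7-87.4%. For 1/1.2 the values are 73.6-74.5% (MHI-5) and 82.6-83.5% (medication). With 34.4% exposed, from 778/(778 + 1,485) under Transitions Between Work Categories, the pooled formula gives 81% or more in all four cases. The stated power is thus broadly reproduced. Because the exposed share is unstated, it is not called wrong.

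**Step 2: how often the rule flags a true 20% bias.** Let the true medication OR be 1.2 times the MHI-5 OR. The rule fires if the two estimates have opposite signs and at least one has |z| > 1.96. When both true ORs exceed 1, this needs essentially the MHI-5 estimate to fall below 1, with probability Φ(−ln OR/SE). At OR 1.2 that is Φ(−0.1823/0.0654) = 0.27%; at 1.1 it is Φ(−0.0953/0.0664) = 7.6%; at 1.05 it is Φ(−0.0488/0.0670) = 23%. Simulation of the full rule gives:

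| MHI-5 OR | Medication OR | Flagged | Unflagged |
|---|---|---|---|
| 1.2 | 1.44 | 0.3% | 99.7% |
| 1.1 | 1.32 | 7.5% | about 92% |
| 1.05 | 1.26 | 22-23% | about 77% |
| 1.0 | 1.2 | 42-44% | 56-58% |

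Other patterns: masking at 1.44/1.2 is flagged 0.1% of the time, complete masking at 1.2/1.0 37-40%, and truly opposite ORs (0.833/1.2) 96-98%.

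**Step 3: what a direct contrast would give.** SE of the log ratio = √(s1² + s2² − 2ρ·s1·s2). For 1.2/1.44, s1 = 0.0654 and s2 = 0.0572.

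- ρ = 0: SE 0.0869, 95% CI factor exp(1.96 × 0.0869) = 1.19, power Φ(0.1823/0.0869 − 1.96) = 55%.
- ρ = 0.3: SE 0.0728, CI factor 1.15, power Φ(0.1823/0.0728 − 1.96) = 71%.

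For 1.0/1.2 the SEs are 0.0896 and 0.0751, and the powers 53% and 68%. Over the four rows of the table, power is about 53-71% and the CI factor 1.15-1.19.

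**The case against.** The strongest defence is that the rule answers a directional question and says so. What it contradicts is reading a raised or lowered rate of medication as a raised or lowered rate of poor mental health. Two ORs on the same side of 1 do not mislead on that. The text is hedged, never claims that silence proves negligible bias, and both ORs with their CIs will be reported, so a large gap would be visible. This stands, and it is why the sign rule is worth keeping. It does not meet the negligibility condition, however, and two separate CIs do not give the CI of the ratio when both estimates come from the same people.

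A second objection also stands in part: the ratio of the two ORs is not a pure measure of care-seeking. MHI-5 covers four weeks and has no sleep item. Medication is counted over a calendar year, and hypnotics and sedatives made up 32.07% of new cases in 2001 (Discussion). The ORs could differ without any prescription bias.

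Third, a reader might ask for a fixed pass limit or for the three primary hour categories. The article does not compel either. If the true ratio is 1 (both ORs 1.0), the chance that the 95% CI lies within 1/1.2 to 1.2 is about 4% at ρ = 0 (SE 0.0908) and 2Φ(0.1823/0.0761 − 1.96) − 1 = 34% at ρ = 0.3. A split widens the CI further. For 41-48 hours (26.7 − 10.5 = 16.2% of workers, against 73.3% unexposed) the SE grows by √[(1/16.2 + 1/73.3)/(1/26.7 + 1/73.3)] = 1.21, so pooled SEs of 0.075-0.090 give CI factors of about 1.20-1.24. Pooling above 40 hours is a defensible choice for power.

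**Conclusion.** The concern holds in this form: the article makes a morbidity reading conditional on showing negligible bias, and its only rule cannot show it. How often a 20% bias escapes depends on the true MHI-5 OR, from about 99.7% at 1.2 to 56-58% at 1.0.

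Two stronger readings are tempting and are not supported. One is that the rule misses a 20% bias almost every time; that holds only when the MHI-5 OR is about 1.1 or more. The other is that bias able to create or hide the whole of a 1.2 effect would normally pass unnoticed. It is flagged 42-44% of the time when it creates the effect and 37-40% when it hides it: poor, but far from never.

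The primary endpoint, model and test are untouched, and the article regards an association with medication use as of interest in itself. The gap concerns interpretation, chiefly of effect size. The percentages are illustrative. They rest on the DWECS 2000 exposed share, the assumed correlation, and no allowance for covariates or repeated measurements.

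**What to change.** Before linkage:

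- Keep the sign rule, described as a check on direction.
- Add one stacked GEE logistic model with both outcomes per interview, person as the cluster, and an interaction of outcome type with working hours (more than 40 versus 32-40 hours). Report the ratio of the medication OR to the MHI-5 OR with its 95% CI from empirical standard errors.
- State that absence of a contradiction does not establish negligible prescription bias, and that the size of the primary rate ratio is reported as medication use unless the ratio and its CI support a morbidity reading.
- Note that the ratio also reflects the different time windows and constructs, including the missing sleep item in MHI-5.

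The cost is some wording and one extra model on data already planned. The downside is precision: with a CI factor of about 1.15-1.19 and power of about 53-71% for a 20% discrepancy, the morbidity reading may often remain unsupported, and the authors should be ready to report medication use only.

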### The Danish Government and Increased Working Hours

The Danish government wants to increase the total number of work hours in the nation by: (1) decreasing the number of hours that are lost due to sickness absence and early retirement, and (2) encouraging the ones that are working, to work longer hours [18]. From this perspective, we want to know if there is a positive, negative, or no correlation between long working hours and incidence of psychiatric disorders in the Danish working population, in other words, if pathogenic effects of long working hours outweighs the salutogenic effects or vice versa. We are especially interested in the situation among the people who perform moderate overtime work (41-48 work hours/week), that is, overtime work which lies within the limits of the European working time directive. If there is a nonnegligible correlation between long working hours and subsequent mental ill health, then this needs to be taken into account in the planning and evaluation of strategies aimed at getting more people to work extra hours.

The existing literature does not provide the information we need to settle this question.

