## Discussion

### The Research Project

This protocol gives a detailed plan for a research project aimed at investigating the possibility of a prospective association between weekly working hours and use of psychotropic medication in the general working population of Denmark. We have shown that the statistical power is sufficient, and that the exposure is stable enough to make the study worth the while. We have also designed an auxiliary study, which will help us to interpret the results of the primary analysis, which, a priori, might be affected both by differences in morbidity and differences in propensity to seek treatment.

The presented study will utilize the work hour categories proposed by Kleppa et al [19], that is, 32-40 to represent normal weekly working hours, 41-48 to represent overtime work which lies within the limits of the European working time directive, and 49-100 to represent overtime work beyond the threshold of the directive. These cut-off points will enable us to evaluate the results from a societal (national burden of disease) perspective, since they allow us to answer the following questions, “Are there important differences between the average rate among people with normal working hours, and that among people with overtime work within and beyond the EU directive, respectively?”. The span of the maximum work hour category complicates, however, the interpretation of the results from an individual perspective. A null finding, which would indicate that the effect is unimportant from a societal perspective, does not necessarily mean that it is safe to work, for example, 60 hours or more per week. From this viewpoint, we understand that an extra work hour category would be of interest, especially to people in nations where it is normal to work 50 hours (or more) per week. An extra category would, however, reduce the statistical power of the analysis, and we prefer to have one sufficiently powered category (> 48 hours), instead of two underpowered categories (eg, 49-59; ≥ 60 hours).

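### The prescription-bias check pools all overtime above 40 hours, so it does not say separately for 41-48 and >48 hours whether the morbidity reading is contradicted

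*Protocol article*

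**What the plan says.** Under Statistical Model, the Protocol article analyses incidence rates "as a function of weekly working hours (32-40; 41-48; > 48 hours/week". The model therefore yields two rate ratios, each against 32-40 hours. The Introduction gives one of them priority: "We are especially interested in the situation among the people who perform moderate overtime work (41-48 work hours/week". The Discussion (The Research Project) defends the cut-offs because they let the normal-hours rate be compared with "that among people with overtime work within and beyond the EU directive, respectively".

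Under Auxiliary Analysis Regarding Prescription Bias, the article sets a condition on interpretation: "Obtained rate ratios can, however, only be interpreted as morbidity rate ratios if we can show that prescription bias is likely to be negligible". The analysis offered for this compares two odds ratios, one for poor self-rated mental health (MHI-5 of 52 or less) and one for use of psychotropic medicine. The exposure has two levels: "Logistic regression will be used to model the odds of the outcomes as a function of weekly working hours (>40 hrs/week; 32-40 hrs/week". The morbidity reading counts as contradicted under this rule: "If either of these ratios is statistically significant, while the other one points in the opposite direction". No three-level version is planned, and no reason is given for collapsing the two overtime groups.

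**The concern.** The condition applies to the rate ratios the study obtains, and the primary model obtains two. The check examines their mixture. If willingness or opportunity to seek treatment differs between people at 41-48 hours and people above 48, the pooled comparison can go wrong in two ways. It can look concordant while one category is discordant. It can also declare a contradiction that comes from >48 hours and casts doubt on 41-48, the category of special interest.

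The primary estimates and their test are not affected. What is at stake is whether each rate ratio may be described as a difference in morbidity or only as a difference in medicine use.

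**Working it through.** **Inputs.** N = 16,500, with prevalence 7.3% (poor mental health) and 9.3% (medicine use), from the auxiliary section. Exposed shares come from Power Calculations (DWECS 2000): 26.7% above 40 hours and 10.5% above 48, hence 16.2% at 41-48 and 73.3% at 32-40. The article does not state the exposed share of the auxiliary sample, so 26.7% is an assumption. As an alternative I use 778/2263 = 34.4%, from the 2000-2005 transition table (people aged 30 or over), with the same split between categories.

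**Who makes up the pooled group.** 16.2/26.7 = 61% work 41-48 hours and 10.5/26.7 = 39% work more than 48.

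**The article's own power figure (at least 80% at OR 1.2 or 1/1.2).** With p1 = OR·p0/(1 − p0 + OR·p0), and p0 chosen so that the stated prevalence holds overall:

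- SE = √[1/(n1·p1(1 − p1)) + 1/(n0·p0(1 − p0))]
- power = Φ(|ln OR|/SE − 1.96)

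For >40 versus 32-40, n1 = 4,405 and n0 = 12,095. For poor mental health at OR 1.2, p0 = 0.0696, p1 = 0.0824 and SE = 0.0654, so power = Φ(0.1823/0.0654 − 1.96) = 80%. The other cells are 74% (poor mental health, OR 1/1.2), 87% (medicine, OR 1.2) and 83% (medicine, OR 1/1.2). At a 34.4% share the four cells are 80-91%.

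**The same formula by category, each against 32-40:**

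| Contrast | Poor mental health, OR 1.2 / (1/1.2) | Medicine, OR 1.2 / (1/1.2) |
|---|---|---|
| 41-48 (n = 2,673) | 64% / 56% | 74% / 65% |
| >48 (n = 1,732) | 50% / 41% | 58% / 49% |

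At a 34.4% exposed share the ranges are 64-80% for 41-48 and 49-67% for >48.

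**How the contradiction rule behaves.** I simulated the rule with hypothetical ORs, the shares above, reference prevalences 7.3% and 9.3%, independent outcomes, no covariates and no repeated measures.

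1. *Discordance only above 48 hours.* Poor mental health OR is 1.15 in both categories; medicine OR is 1.15 at 41-48 and 0.80 at >48. Medicine prevalence is 0.1055 at 41-48 and 0.0758 at >48. The mixture is 0.607 × 0.1055 + 0.393 × 0.0758 = 0.0938, a pooled OR of (0.0938/0.9062)/(0.093/0.907) = 1.01. The pooled rule flags about 26% of the time and the >48 check about 71%.
2. *Contradiction driven by >48 hours.* Poor mental health OR is 1.2 in both; medicine OR is 1.05 at 41-48 and 0.75 at >48. The pooled medicine OR is 0.93. The pooled rule flags about 75% of the time, although both true ORs at 41-48 lie above 1.
3. *Same discordance in both categories.* Poor mental health OR is 1.2; medicine OR is 1/1.2. The pooled rule flags 96%, the 41-48 check 87% and the >48 check 72%.
4. *No effect and no bias.* One check gives a false contradiction with probability (1 − 0.95²)/2 = 4.9%. For at least one of two checks, treated as independent, it is 1 − (1 − 0.049)² = 9.5%; simulation with the shared reference group gives 9.4%.

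**The case against.** The pooled contrast belongs to the plan. The aim is worded as long versus normal hours, the transition table uses the same split, Power Calculations lists >40 versus 32-40 among its contrasts, and a >40 summary can be formed from the three-level model. The choice also has a visible rationale. The article claims at least 80% power for the pooled contrast, and the Discussion prefers one adequately powered category to two weak ones, although that remark concerns splitting the group above 48 hours. If prescription bias is similar in both categories, the pooled rule is the better detector (case 3), and two category rules nearly double the false contradictions (case 4). Nothing in the article says that bias is confined to >48 hours.

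All of this stands, and it is why the pooled check should remain the main one. It does not supply the separate answers that the Introduction and Discussion ask for.

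Three stronger readings are tempting but unsupported:

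- *A reader might infer that the pooled check is uninformative about the two rate ratios.* It is informative, mostly about 41-48 hours.
- *A reader might infer that the plan transfers a favourable verdict to both rate ratios.* The stated rule is one-way: discordance contradicts the morbidity reading, and nothing says that absence of discordance establishes it.
- *A reader might infer from the 74% cell that the 80% power claim is wrong.* That cell depends on an exposed share the article does not state, and it reaches 80% at 34.4%.

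**Conclusion.** The point holds in a limited form. The check does not say separately for 41-48 and >48 hours whether the morbidity reading is contradicted, yet these are the two rate ratios the primary model estimates and the condition on interpretation covers. Depending on the pattern, pooling can miss discordance above 48 hours (flagged about 26% of the time against about 71%) or flag a contradiction (about 75%) when 41-48 is concordant. These figures rest on invented ORs, a 26.7% exposed share, independent outcomes and no covariates. They show that the coding can matter, not that such bias is present. The change is worth making before linkage, because the article relies on its models being fixed by then.

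**What to change.** Keep >40 versus 32-40 and its contradiction rule as the main check. In addition:

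- Fit both auxiliary logistic models with the primary exposure levels (32-40; 41-48; >48).
- Report the poor-mental-health and medicine ORs with 95% CIs for each overtime category, as supporting evidence.
- State in advance that, where the category pairs differ, the morbidity reading is limited to the category they support.
- State that a non-significant category result does not show that bias is negligible.

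The work is two extra model fits on data already assembled. The statistical price is the lower category-specific power shown above and, if the contradiction rule were applied to both categories, a chance of at least one false contradiction of about 9.5% instead of about 5% when there is no effect. Category results should therefore be read from their intervals.

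### The auxiliary analysis claims at least 80% power for both outcomes; carrying over the plan's 26.7% exposed share, MHI-5 at OR 1/1.2 reaches only about 74–77%, and the share and unit of N are unstated

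*Protocol article*

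**What the plan says.** The section on prescription bias plans two logistic models fitted by generalized estimating equations (GEE), comparing more than 40 with 32–40 weekly hours. One outcome is poor self-rated mental health (MHI-5 of 52 or less), the other is redemption of a psychotropic prescription.

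- Size: "Approximately 16,500 employees will fulfill the inclusion criteria of this auxiliary analysis".
- Prevalences: "The prevalence of poor self-rated mental health (MHI-5 ≤ 52) among Danish employees was estimated to 7.3% in 2008", while "the corresponding prevalence for use of psychotropic medicine was 9.3" per cent.
- Test: "An OR will be considered statistically significant if the CI does not contain 1". The interval is a 95% CI, so this is two-sided 0.05.
- Power: "we estimate that the power to detect an OR of 1.2 or higher or 1/1.2 or lower between employees with long versus normal". The figure given is 80% or more, for each outcome.

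The section gives no share of exposed workers. The only share given for all people working 32 or more hours is in Power Calculations, from the 2000 DWECS wave: "26.7% worked more than 40 hours/week and 10.5% worked more than 48 hours/week".

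**The concern.** The power statement is a floor over two outcomes and two directions, so it is only as good as its weakest case. That case is the rarer outcome (MHI-5, 7.3%) with an odds ratio below 1, where the smaller, exposed group also has fewer events. It is not a remote case, because the Introduction argues that long hours may have protective effects.

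What is at stake is interpretation. The protocol will read rate ratios as morbidity ratios only if prescription bias can be shown to be likely negligible. Its rule declares a contradiction only when one of the two odds ratios is significant and the other points the opposite way. Lower power makes a contradiction harder to find, so an overstated figure lends unearned weight to a finding of no contradiction.

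**Working it through.** **Inputs.** N = 16,500, treated as independent observations. Two-sided alpha 0.05. Overall prevalence 7.3% (MHI-5) and 9.3% (medication), all from the auxiliary section. Exposed share q = 0.267, carried over from Power Calculations. Hence n1 = 0.267 × 16,500 ≈ 4,406 exposed and n0 ≈ 12,094 unexposed.

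**Cell probabilities.** Solve q·p1 + (1 − q)·p0 = prevalence with [p1/(1 − p1)] / [p0/(1 − p0)] = OR. For MHI-5 at OR 1/1.2: p0 = 0.0762, p1 = 0.0643, difference D = 0.01188.

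**Three two-sided formulas for that case.**

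1. Wald on log OR: SE = √[1/(n1·p1(1 − p1)) + 1/(n0·p0(1 − p0))] = 0.0703. ln 1.2 / SE = 0.1823/0.0703 = 2.59. Power = Φ(2.59 − 1.96) = 73.6%.
2. Pooled two-proportion test: null SE = √[0.073 × 0.927 × (1/n1 + 1/n0)] = 0.00458, alternative SE = 0.00441. Power = Φ[(0.01188 − 1.96 × 0.00458)/0.00441] = 74.5%. A simulation with 400,000 replicates also gave 74.5%.
3. Unpooled two-proportion test: Φ(0.01188/0.00441 − 1.96) = 76.8%.

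**All four cases, same inputs:**

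| Outcome | OR | Wald | Pooled | Unpooled |
|---|---|---|---|---|
| Medication, 9.3% | 1.2 | 87.4% | 86.7% | 85.2% |
| Medication, 9.3% | 1/1.2 | 82.6% | 83.5% | 85.2% |
| MHI-5, 7.3% | 1.2 | 79.6% | 78.8% | 76.8% |
| MHI-5, 7.3% | 1/1.2 | 73.6% | 74.5% | 76.8% |

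The claim is reproduced for medication, so the method is not unduly severe. If 7.3% is taken as the unexposed prevalence, MHI-5 at 1/1.2 gives 71.9%, 72.8% and 75.2%, and MHI-5 at 1.2 rises to as much as 81.3%.

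**Sensitivity of MHI-5 at 1/1.2 to the exposed share (Wald / pooled / unpooled):**

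- 26.7%: 73.6 / 74.5 / 76.8%
- 30% (assumed): 77.0 / 77.8 / 79.6%
- 34.4%: 80.4 / 81.1 / 82.4%. This share is 778/(778 + 1485), from Transitions Between Work Categories.

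**What 80% would need at a 26.7% share.** About 18,850 (pooled) to 19,300 (Wald) independent observations, or, at 16,500, an odds ratio of about 1/1.22 = 0.82.

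**Readings that reach about 80% at 26.7%.** One-sided testing (83.8%), treating 1/1.2 as a risk ratio (80.4%), or taking 7.3% as the prevalence among the exposed (79–81%). The text supports none of them: it specifies a 95% CI, an odds ratio, and a prevalence among employees in general.

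**The case against.** The best defence is that the shortfall rests on two inputs the auxiliary section does not fix.

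*Exposure share.* The 26.7% is one wave, quoted for another analysis, whereas the auxiliary pool is DWECS 1995, 2000 and 2005 plus DANES 2008. At 34.4% the claim holds. But that share comes from people aged 30 or older who were economically active in both 2000 and 2005, which is not the auxiliary population. It shows that the result is sensitive to the share. It does not supply the right one.

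*Unit of N.* If 16,500 counts persons, the GEE has more observations than that. The protocol's person-years give 68,000/17 = 4,000 per DWECS follow-up year and 16,000/4 = 4,000 for DANES. At 25 cases per 1,000 person-years this implies roughly 17,000 non-prevalent people at baseline across the four samples, and 17,000/0.907 ≈ 18,700 once the 9.3% prevalent users are restored. With 18,700 independent observations the weak case reaches 79–82%. Against this, four samples averaging 4,000 give 16,000, so 16,500 may equally be a count of observations, and within-person correlation would take back part of any gain. The point cannot be settled from the text.

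The defence is also right on consequence. The analysis is offered only as a partial check, and its rule can also be triggered by the medication odds ratio, which is adequately powered. The surveys are already collected, so no sample size depends on the sentence.

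A reader might go further and infer that the claim fails for MHI-5 in both directions, or that true power is nearer 70%. The documents do not support either. MHI-5 at OR 1.2 straddles 80%, and the lower figure needs a design effect, such as 1.1, that the protocol does not give. Covariate adjustment and within-person correlation would tend to lower power, but by an amount that cannot be read from the text.

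**Conclusion.** The concern holds in limited form, as a minor point. Under the only exposed share given for the 32-or-more-hours population, and with independent observations, the 80% floor is missed in one case of four. MHI-5 at OR 1/1.2 has about 74–77% power at 7.3% overall prevalence, a shortfall of 3 to 6 points; if 7.3% is the unexposed prevalence the shortfall is about 5 to 8 points. MHI-5 at OR 1.2 is borderline, and medication use meets the claim.

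This is conditional on the 26.7% share and on 16,500 being the number of observations, and plausible alternatives for either would bring the case to about 80%. So the sentence is unsupported by the figures given, but not shown to be wrong under every reading. Nor does it follow that the check on prescription bias is worthless: the medication odds ratio keeps its power, and the primary hypothesis, model and power are unaffected.

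**What to change.** In the auxiliary power paragraph:

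- State the exposure share used, whether 16,500 counts persons or observations, and the formula.
- If the 26.7% share applies, restate power for MHI-5 as about 75% at OR 1/1.2 and about 80% at OR 1.2, before any allowance for covariates and repeated persons. Alternatively, give the odds ratio below 1 that has 80% power, about 1/1.22 = 0.82. If another share or a larger count was used, give it and keep the claim only where it then holds.
- Add a sentence saying that the absence of a contradiction under the rule does not by itself show prescription bias to be negligible.

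The cost is wording only, with one stated figure becoming slightly less favourable. Design, data and primary analysis do not change.
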